## Abstract

**Background:**

Lumbar spine fusion (LSF) effectively decreases pain and disability in specific spinal disorders; however, the disability rate following surgery remains high. This, combined with the fact that in Western countries the number of LSF surgeries is increasing rapidly it is important to develop rehabilitation interventions that improve outcomes.

**Methods/design:**

In the present RCT-study we aim to assess the effectiveness of a combined back-specific and aerobic exercise intervention for patients after LSF surgery. One hundred patients will be randomly allocated to a 12-month exercise intervention arm or a usual care arm. The exercise intervention will start three months after surgery and consist of six individual guidance sessions with a physiotherapist and a home-based exercise program. The primary outcome measures are low back pain, lower extremity pain, disability and quality of life. Secondary outcomes are back function and kinesiophobia. Exercise adherence will also be evaluated. The outcome measurements will be assessed at baseline (3 months postoperatively), at the end of the exercise intervention period (15 months postoperatively), and after a 1-year follow-up.

**Discussion:**

The present RCT will evaluate the effectiveness of a long-term rehabilitation program after LSF. To our knowledge this will be the first study to evaluate a combination of strength training, control of the neutral lumbar spine position and aerobic training principles in rehabilitation after LSF.

**Trial registration:**

ClinicalTrials.gov Identifier NCT00834015

## Background

During the last 10 years there has been a significant increase in the number of lumbar spine fusions (LSF) [1]. The most common reasons for LSF are isthmic or degenerative spondylolisthesis, degenerative disc disease, and spinal stenosis [2]. In adult patients with lumbar isthmic or degenerative spondylolisthesis LSF has been reported to reduce symptoms [3,4]. However, the overall disability of patients after LSF may be high [5] and even 25% of patients rated the overall outcome as unchanged or worse in a 2-year follow-up study [3]. Most of the previous studies on LSF have evaluated the surgical procedure itself or compared conservative treatment to operative treatment. Less information is available on long-term exercise programs for patients after LSF surgery.

The effectiveness of rehabilitation after LSF has only been evaluated in four studies [6-9]. In these studies, the timing of the intervention has differed. In the studies of Nielsen et al. [8,9], prehabilitation started 6 to 8 weeks before surgery and continued during hospitalization. Abbott et al. [6] evaluated the effectiveness of psychomotor therapy implemented during the first 12 postoperative weeks. A Danish study [7] compared three different postoperative rehabilitation programs lasting between 12 and 20 postoperative weeks.

Exercise was an essential component of the rehabilitation protocols in all the LSF rehabilitation studies; however the guidance and exercise methods used were different. In the studies of Nielsen et al. and Christensen et al. [7-9], exercise programs included muscle endurance and strength training for the back and abdominal muscles, and cardiovascular conditioning. In the study of Abbott et al. [6], the exercise program consisted of motor relearning training of the transversus abdominis and multifidus, with cognitive and behavioral elements also integrated into the program. The results of these studies indicate that exercise may improve the outcome of LSF.

Typically, patients with lumbar isthmic or degenerative spondylolisthesis undergoing LSF have suffered low back pain for years and therefore may exhibit changes in the function [10] and structure of their trunk muscles [11], and in their cardiorespiratory condition [12]. LSF itself causes changes in the biomechanics of the lumbar spine, which may also accelerate degenerative changes in the adjacent segments [13] and cause muscle atrophy, leading to fatty infiltration of the lumbar muscles, especially in the multifidus[14-16]. As a possible consequence of these changes, low trunk muscle strength levels in patients after lumbar fusion have been reported [17,18].

The primary goals of the post-operative rehabilitation program are to control pain, decrease disability, restore back function, improve health related fitness and learn to use the low back during the healing process. Although the existing evidence supports the use of exercise in the rehabilitation of LSF patients, there is no consensus on the content of an exercise rehabilitation program after LSF. In addition, the durations of earlier interventions have been too short to achieve long-term changes in back function. Thus, there is a need to develop and test multifaceted rehabilitation programs to improve both back-specific and overall outcome after LSF. In contrast with previous exercise interventions for LSF patients, this study is novel in its development of a fusion-specific training program that takes into account changes in the biomechanics of the spine.

The main study questions are:

· Is combined back-specific and aerobic training more effective in decreasing back pain and disability than conventional instructions in postoperative rehabilitation?

· What are the effects of surgery and training on trunk muscle strength and mobility of the spine?

· What is the effect of fear of movement on post-operative exercise adherence, physical activity, pain and disability?

## Methods/design

### Study design

Figure 1 presents a flowchart of the study. The present randomized controlled trial will be conducted in Tampere University Hospital and the Central Finland Central Hospital. Approval of the study protocol was given by the Ethics Committee of the Central Finland Health Care District in 2008 (Dnro 4E/2008) and by the Ethics Committee of Tampere University Hospital in August 2008. Written informed consent will be obtained from all patients prior to participation.

**Figure 1 F1:**
[figure not shown]
Flowchart of the study.

### Participants

#### Inclusion criteria

All patients aged over 18 years scheduled to undergo elective LSF surgery for isthmic or degenerative spondylolisthesis in Tampere University Hospital or the Central Finland Central Hospital are eligible for the study. Patients will be recruited by the spine surgeons in each hospital.

#### Exclusion criteria

Patients with severe cardiorespiratory or musculoskeletal disease, severe psychiatric/psychological disorder, extensive lower limb paresis, social reasons (alcohol abuse), and immediate complications after back surgery (infection) will be excluded from the study.

### Surgery procedures

Spine surgeons will make the decision to operate according to their normal practice. The surgical procedure to be used is decompression and instrumented posterolateral fusion (PLF) with or without posterior lumbar interbody fusion (PLIF).

### Randomization and blinding

After surgery, the participants will be randomized into either the combined back-specific (combination of strength training and training of control of the neutral lumbar spine position) and aerobic training arm or to the control arm. The allocation will be based on computer randomization in blocks of four patients. The randomization will be performed and the randomization lists maintained by the research nurses, who will not be involved in the assessment or treatment of the participants. The first list will be used to randomize the participants with isthmic spondylolisthesis and the second list to randomize those with degenerative spondylolisthesis. Both centres will have their own randomization lists. Assessors will be blind to the treatment group in both study centres. Physiotherapists will not be blind to group membership; instead, but both study arms will have their own physiotherapist who will carry out postoperative guidance. Blinding the patients to the allocation is not possible due to the nature of the intervention.

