## Statistical analysis

### Sample size

Cristensen et al. [7] estimated that a sample of ~60 patients (30 per group) is necessary to achieve 85% power for detecting a 25% difference in disability over time (baseline to 1 year), or at a follow-up of a 1 year, with a one-sided significance α-level of 0.05. However, we assume the between-group difference in pain will be lower in our participants. Assuming a dropout rate of 15-20% at the 1-year follow-up, we aim to include at least 80 patients (preferably 100) in our sample.

The clinical outcome variables will be analyzed by the intention-to-treat principle with the last observation carried forward (LOCF). The normality of variables will be evaluated by the Shapiro-Wilk statistic. Statistical comparison between the arms will be done using the chi-square test, Fisher's exact test, bootstrap-type analysis of covariance (ANCOVA) or multivariate analysis of variance (MANOVA) with Pillai’s trace statistics. A multiple imputation (Markov-chain Monte Carlo) method will be applied to supply possible missing values of individual questionnaire items, when appropriate.

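### A single published block size of four could let up to a third of allocations be deduced in this open-label trial; randomly varied, undisclosed block sizes would remove most of that at almost no cost

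*Protocol article*

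**What the plan says.** Under Randomization and blinding, the protocol article states: "The allocation will be based on computer randomization in blocks of four patients". No other block size is mentioned. The lists are split by diagnosis ("The first list will be used to randomize the participants with isthmic spondylolisthesis and the second list to randomize those with degenerative spondylolisthesis") and by hospital ("Both centres will have their own randomization lists"), which makes four lists.

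The same section describes who can see the arms. On patients: "Blinding the patients to the allocation is not possible due to the nature of the intervention". Physiotherapists are not blinded either, and "both study arms will have their own physiotherapist who will carry out postoperative guidance". Assessors are said to be blind. The section also gives a safeguard: the randomization is done and the "randomization lists maintained by the research nurses, who will not be involved in the assessment or treatment of the participants".

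Other sections bear on timing. Spine surgeons recruit among patients already scheduled for surgery (Inclusion criteria). Early surgical complications such as infection are a reason for exclusion (Exclusion criteria). Randomization follows surgery, but no date is given. Early postoperative advice is alike in both arms (Preadmission clinic and early postoperative rehabilitation), and the arms diverge at three months (Study arms). On numbers, the Sample size section says "we aim to include at least 80 patients (preferably 100) in our sample".

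**The concern.** In a block of known size, the last allocations follow from the first. Here the size is constant and in print. Once a patient begins arm-specific guidance, the physiotherapist who gives it reveals the arm. Staff who keep track of one list could then sometimes know the next assignment before that patient is entered.

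This matters because one eligibility decision still lies after surgery. If the person making it can foresee the arm, a borderline patient can be excluded or delayed selectively. The primary outcomes (pain, disability, quality of life) are reported by patients who know their arm, so the comparison depends heavily on an allocation that nobody could foresee.

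**Working it through.** The article gives no predictability figure, so there is nothing of its own to reproduce.

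**Inputs**
- Block size 4, two arms (Randomization and blinding).
- Ratio 1:1, so 2:2 within a block. This is an assumption; the ratio is not stated, but it fits a block of four and the planning figure of 30 per group.
- Four lists: 2 diagnoses × 2 centres.
- Total 80 to 100 patients, so 20 to 25 per list on average. The actual split is not given.

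**Share known with certainty, complete blocks**
- A 2:2 block has 6 possible sequences.
- The 4th allocation is always determined: 1 per block.
- The 3rd is determined when the first two are equal, which is 2 of 6 sequences: 1/3 per block.
- Share = (1 + 1/3)/4 = 33.3%.

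**Incomplete last blocks.** A list of 25 has 6 complete blocks and one patient over: 6 × 4/3 = 8 determined, and 8/25 = 32.0%. Simulating four lists with random list sizes gives 31.3% for 80 patients (about 25 patients) and 31.7% for 100 (about 32 patients). Unequal lists (40/30/20/10%) give 31.2% and 31.6%, so the split hardly matters.

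**Best guess rather than certainty.** The chance of guessing right at positions 1 to 4 is 1/2, 2/3, 2/3 and 1. The sum is 17/6, and divided by 4 this is 17/24 = 70.8%, against 50% by chance.

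These figures all require an observer who knows the block size and every earlier allocation in that list at the time the next patient is randomized.

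**Effect of a delay before the arm becomes visible.** The simulation used 100 patients, four lists of equal expected size and even accrual. Accrual time and delay are assumptions; the article gives neither.

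| Accrual | 1-month delay | 3-month delay |
|---|---|---|
| 24 months | 13.5% | 2.2% |
| 36 months | 18.2% | 5.4% |
| 48 months | 21.1% | 8.8% |

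A three-month delay corresponds to randomization just after surgery with the arm showing only when arm-specific care begins. Randomization at about three months means almost no delay and a share close to 31% to 32%. So would telling patients or staff the arm as soon as it is drawn.

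**With other block sizes**
- Known fixed blocks of six: 1/4 certain. Known fixed blocks of eight: 1/5.
- Randomly varied sizes, 25 patients per list, observer knows the possible sizes and all earlier allocations: 5.6% for 4/6 and 2.2% for 4/6/8. Fixed fours give 31.9% in the same simulation.

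**The case against.** The strongest reply is that the figure describes an observer whom the article does not show to exist. Research nurses with no part in treatment or assessment hold the lists, so the sequence is kept from surgeons, physiotherapists and assessors. Recruitment comes before surgery and therefore before allocation. Early care does not reveal the arm. The only exclusion tied to events after surgery is narrow. All of this stands, and it is why one third is a ceiling and not an estimate. What it does not do is prevent deduction: concealing a list does not stop someone from inferring its next entry from past assignments and a published block size.

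The timing limits the risk further. Early complications are a live question soon after surgery, when few recent allocations are yet visible. Near three months, when more are visible, that question should mostly be settled. The article dates neither the randomization nor the exclusion decision, so an overlap cannot be ruled out.

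Three stronger readings are tempting, and the article does not support them:

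- *A third of this trial's allocations will be predictable.* That needs full and immediate knowledge of each list, which is not shown.
- *Assessor blinding is at risk through the blocks.* To deduce an arm, an assessor would already have to know other patients' arms and their order. Blinding would then have failed by another route, and the article says assessors are blind.
- *Four small lists make it worse.* The number of lists does not raise the share per block. Incomplete blocks lower it slightly, and an observer must follow each list separately.

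**Conclusion.** The point holds as a modest design weakness. The article contains no error or contradiction here; it fixes a more predictable method than it needs. Under 1:1 allocation, at most one third of allocations (31% to 32% with incomplete last blocks) could be known in advance with certainty. The real share depends on when randomization takes place after surgery. It could be a few percent if that is soon after the operation, and near the upper bound if it is around three months. The low end rests on assumed accrual of 24 to 48 months and on arms staying hidden until arm-specific care starts. The practical exposure is mainly the exclusion decision after surgery, not initial recruitment and not the blinded assessments.

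**What to change.** - Generate the four lists with randomly varying block sizes, for example 4 and 6, or 4, 6 and 8. Adding blocks of two is less effective: 2/4/6 leaves 3.6% certain, against 2.2% for 4/6/8.
- Say in site documents only that block sizes vary, and do not disclose the sizes to site staff.
- Have the research nurses release each assignment only after eligibility following surgery is confirmed and the patient is irrevocably entered, and state when that is.

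The cost is regenerating the lists (or their unused remainder, if randomization has begun) and slightly larger possible imbalance. An unfinished block can leave a list out of balance by at most half the block size: 2 patients with fours, 3 with sixes, 4 with eights. Over four lists the worst case is 4 × 2 = 8, 4 × 3 = 12 or 4 × 4 = 16, and it arises only if every list stops at its worst point in the same direction. Varied sizes remove most of the certainty but not all of the guessing advantage: even known blocks of eight allow 66.6% correct guesses. The rule on releasing assignments is therefore needed as well.

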### Preadmission clinic and early postoperative rehabilitation before the intervention

At the preadmission clinic, patients will meet with the spine surgeon, anesthesiologist, and physiotherapist, and be informed about the operation and rehabilitation. The early postoperative mobilization of the patients in the orthopaedic ward will be carried out by the physiotherapist. During the first three post-operative months, patients will be encouraged to walk and perform light abdominal, back, and thigh muscle exercises; stretching of hip muscles will also be included in the exercise program. The early postoperative exercise instructions will be similar for both study arms. The use of a bicycle ergometer will be allowed one month after the operation. Other types of exercise such as skiing, dancing, and water gymnastics will be permitted two months after surgery.

### Study arms

The intervention arms will start three months postoperatively and will last 12 months.

### Development of the intervention arm program

In the development of the protocol for the intervention arm, we have used information obtained from our own trunk muscle electromyography studies, conducted among healthy subjects [19,20] and lumbar fusion patients ([name] et al., unpublished observation), other previously published studies on trunk and hip muscle activation during exercises [21-24], as well as information from a multidisciplinary group in the study hospitals (physiotherapists, nurses, spine surgeons), and feedback from patients regarding the feasibility of the program. The timing of the beginning of intervention is based on recovery from the surgery.

The back-specific exercise program has two main aims: (i) to improve control of the neutral lumbar spine position and (ii) increase trunk and hip muscle coordination, strength, and endurance [25-29]. (Table 1).

**Table 1 T1:** Back-specific exercises program

**Phase**	**Back specific exercises**	**Goal of the exercise**
I	1. Squat (SP, EB)	MS
	2. Abdominal crunch (SUP)	ME
	3. Hip abduction (CLP)	CNSP
	4. Hip abduction and external rotation (SLP, EB)	CNSP/ME
	5. Hip extension (PRO)	CNSP
	6. Hip extension (FPKP, EB) Sets x Repetitions: 2 x 10-15-20	CNSP/ME
II	1. Squat (SP, EB)	MS
	2. &3. Bilateral shoulder extension and flexion (SP, EB)	ME/MS
	4. Heel slide or leg lift and knee extension with one leg (SUP)	CNSP
	5. Hip extension or hip extension and knee extension (CLP)	CNSP/ME
	6. Hip abduction (SLP, EB)	CNSP/ME
	7. Hip extension (EB) or bird dog exercise (FPKP) Sets x Repetitions: 2 x 10-15-20	CNSP/ME
III	1. Squat (SP, EB)	MS
	2. & 3. Bilateral shoulder extension and flexion (SP, EB)	ME/MS
	4. Leg lift and knee extension with one leg (SUP)	CNSP
	5. Hip extension and knee extension (CLP)	CNSP/ME
	6. Bird dog exercise (FPKP)	CNSP/ME
	7. Hip abduction (SP) Sets x Repetitions: 2–3 x 10-15-20	CNSP/ME
IV	1. Squat (EB) or forward lunge (SP)	MS
	2. Waiters bow exercise with elastic band (SP, EB)	MS
	3. & 4. Bilateral shoulder extension and flexion (SP, EB)	ME/MS
	5. & 6. Unilateral shoulder horizontal adduction and abduction (SIP, EB)	CNSP/ME
	7. Hip abduction (SP, EB) Sets x Repetitions: 2–3 x 10-15-20	CNSP/ME
V	1. Forward lunge (SP)	ME/MS
	2. Waiters bow exercise (SP, EB)	MS
	3. & 4. Unilateral shoulder horizontal adduction and abduction (SP, EB)	CNSP/ME
	5.& 6 Downward chop and upward chop (SIP, EB)	CNSP/ME
	7. Hip abduction (SP, EB) Sets x Repetitions: 2-3-4 x 10-15-20	CNSP/ME
VI	1. Forward lunge (SP)	ME/MS
	2. Waiters bow exercise (SP, EB)	MS
	3. & 4. Unilateral shoulder horizontal adduction and abduction (SP, EB)	CNSP/ME
	5. & 6. Downward chop and upward chop (SP, EB) Sets x Repetitions: 2-3-4 x 10-15-20	CNSP/ME

SP, standing position; SUP, supine position; CLP, crook lying position; SLP, side lying position; PRO, prone position; FPKP, four-point kneeling position; SIP, sitting position; EB, with elastic band resistance; MS, muscle strength; ME, muscle endurance; CNSP, control of the neutral lumbar spine position.

At the beginning of the program, trunk and hip muscle coordination and muscle endurance exercises will be performed in a prone, supine and four-point kneeling position. During the intervention the performance positions will gradually become more functional [30] and the loads increase progressively up to 50-70% of the repetition maximum to optimize muscle strength and muscle mass development. A subset of these exercises will be carried out with light loads to improve explosive force (high-velocity repetitions) and movement control. In addition, muscle-fatiguing training will be used for the back muscles to produce regional increases in blood flow capacity among the muscle fibers that experience increased activity during loading. Participants will be instructed to perform home exercises at least 2–3 times per week.

The aerobic walking program has three aims: (i) to increase the total amount of physical activity [31], (ii) improve patients’ aerobic capacity, and (iii) increase muscle capacity for fatty acid oxidation [32,33]. The program includes a progressive increase in the number of steps and interval walking workouts.

The total activity level will be evaluated during the first week by pedometers. Based on this information, patients will be instructed to increase their activity level progressively and monitor the amount of daily steps with the pedometer. (Table 2). Interval walking will be added to the exercise program four months after the beginning of the intervention. Each interval exercise consists of 5–10 minutes warm-up at normal walking speed, followed by periods of 30s - 1 min of brisk walking and 3 min of walking at normal speed alternated four times. The total length of the exercise bout will be 25–30 minutes. The length and intensity of brisk walking will be gradually increased during the last eight months.

**Table 2 T2:** Aims for increasing the number of daily steps

**Aim**	**Model of progression**
10 000 steps/day, if: age under 65 years, healthy and no restrictions to increase physical activity	1. If baseline level <5 000 (sedentary), number of steps is increased 15% every other months until the target level is reached
	2. If baseline level 5 000–7 499 (”low active”), number of steps is increased 10% every other months until the target level is reached
	3. If baseline level 7 500–9 999 (”somewhat active”), number of steps is increased 5% every other months until the target level is reached
	4. If baseline level >10 000 (active), this level is maintained or number of steps is increased 5% every other months until 12 500/day (”highly active”) is reached (Categorized according to Tudor-Locke et al. 2008 [34])
7 500 steps/day, if: age >65 years and/or chronic diseases and/or some restriction to increase physical activity [35,36]	1. If baseline level <4 250, number of steps is increased 15% every other months until the target level is reached. In later phase this level is maintained or a new goal is set.
	2. If baseline level >4 250, number of steps is increased 10% every other months until the target level is reached. In later phase this level is maintained or a new goal is set.

Individual guidance sessions with the physiotherapist will be started three months after the LSF, with booster sessions every second month thereafter. In each session the physiotherapist will give guidance on the exercises to be performed in the next training phase and check the patients’ exercise techniques. In addition, patients will be given a leaflet containing written and pictorial information about the exercises. Each patient will perform the training independently at home; however, the progression of the exercises will be checked with the physiotherapist. During the first session, patients will fill in a personal exercise contract form and set their personal goals [37]. Goals will be reassessed in the middle phase of the intervention. Possible barriers to exercise (e.g. kinesiophobia) will be identified [38,39]. If a patient’s score on the Tampa scale for kinesiophobia (TSK) is over 37 in the post-operative assessment, the physiotherapist will explain to the patient (during the second/third guidance session) how and why some individuals with low back pain may develop a chronic pain syndrome (the fear-avoidance model, [40]). The patient’s experiences of the previous training phase will be reviewed during each guidance sessions. Patients will receive elastic bands (Thera-Band, The Hygenic Corporation, Akron Ohio, USA) and a pedometer (Omron Walking Style II, Kyoto, Japan) for their personal use.

